## Abstract

**Background:** Myocardial fibrosis leads to ventricular dysfunction and worsened prognosis, especially after ST-segment elevation myocardial infarction (STEMI). Sodium–glucose cotransporter 2 inhibitors (SGLT2is) offer cardiovascular benefits by reducing markers of myocardial fibrosis and fibroblast activity. However, the effects of SGLT2i on myocardial fibrosis deposition among STEMI patients undergoing primary percutaneous coronary intervention (PCI) have not yet been evaluated. **Study and Design**: The effect of DAPAgliflozin on myocardial fibrosis and ventricular function in patients with STEMI (*DAPA-STEMI*) trial is a phase III, multicenter, randomized, double-blind, placebo-controlled trial. The study aims to assess the effects of dapagliflozin on myocardial fibrosis and ventricular function, evaluated using cardiac magnetic resonance (CMR), in STEMI patients undergoing primary PCI. Eligible patients were 30 to 85 years old and exhibited a left ventricular ejection fraction ≤ 50%. A total of 120 patients with STEMI were expected to be randomized 1:1 to receive dapagliflozin 10 mg or placebo daily for six months. The primary endpoint is the change in the extracellular volume fraction of the remote myocardium from baseline to six months, as measured by CMR. The secondary endpoints include changes in the circulating C-terminal propeptide of type I procollagen, N-terminal propeptide of type III procollagen, and Galectin-3 from baseline to six months. The study was stopped prematurely due to slow recruitment, with 54 enrolled patients, limiting the statistical power to detect changes in the primary endpoint between groups. **Conclusions:** The DAPA-STEMI trial will provide insights into the impact of dapagliflozin on myocardial fibrosis and ventricular remodeling in patients with STEMI undergoing primary PCI. **Clinical Trial Registration Unique Identifier**: NCT06619600

## 1. Introduction

Myocardial fibrosis is the expansion of the cardiac interstitium by due to the deposition of extracellular matrix proteins. There are two main types of myocardial fibrosis: diffuse interstitial fibrosis and focal replacement fibrosis [1]. Diffuse interstitial fibrosis is the widespread deposition of collagen fibers between myocytes, usually seen in response to chronic conditions such as hypertension or heart failure [1]. On the other hand, focal replacement fibrosis is the deposition of scar tissue that replaces dead or damaged myocytes, often following events like myocardial infarction (MI) [1]. Of note, both diffuse and focal fibrosis contribute to ventricular dysfunction and worsen long-term prognosis [1,2]. Patients with ST-segment elevation MI (STEMI) experience both focal replacement fibrosis in the region of the MI and diffuse interstitial fibrosis in the remote myocardium as interstitial fibrosis is triggered by ischemia and subsequent inflammation [3].

Sodium–glucose cotransporter 2 inhibitors (SGLT2is) provide cardiovascular benefits beyond glucose control, reducing heart failure hospitalizations and cardiovascular mortality in patients with or without type 2 diabetes mellitus (T2DM). Preclinical studies indicate that SGLT2is modulates myocardial fibroblast activity, decreasing fibroblast migration and inhibiting profibrotic pathways [4]. Additionally, in individuals with T2DM and stable coronary artery disease (CAD), SGLT2is have been associated with a reduction in myocardial extracellular volume (ECV), a marker of myocardial fibrosis, as measured by cardiac magnetic resonance (CMR) [5]. However, the effects of SGLT2is in remote myocardial fibrosis and ventricular function in patients with STEMI undergoing primary percutaneous coronary intervention (PCI) have not been studied.

The effect of DAPAgliflozin on myocardial fibrosis and ventricular function in patients with STEMI (DAPA-STEMI) trial aims to assess the effect of dapagliflozin on myocardial fibrosis and ventricular function in patients presenting with their first clinically diagnosed STEMI, compared to placebo, by means of CMR imaging and circulating biomarker assessment.

## 2. Methods

### 2.1. Trial Organization and Sources of Funding

The DAPA-STEMI trial was conceived and designed by the Trial Steering Committee (Supplementary Materials). It is sponsored by the Spanish Society of Cardiology and registered in the European Union Drug Regulating Authorities Clinical Trials Database (EudraCT, 2018-003105-25) and ClinicalTrials.gov (NCT06619600). The lead site is the University Hospital Clinic of Barcelona. Funding for the trial as well as dapagliflozin and the matching placebo is provided by AstraZeneca (ESR-19-14489). The sponsor and funder had no role in the design or conduct of the trial and will not be involved in data analysis or interpretation. The trial protocol and any substantial amendments were approved by the Spanish Agency of Medicines and Medical Devices and the Research Ethics Committee of the University Hospital Clinic of Barcelona (HCB/2018/0960). The current protocol version is 2.1, dated 21 September 2021. Although the study planned to enroll a total of 120 patients, enrollment was terminated early due to slow recruitment, resulting in a final sample size of 54 patients. The study was conducted in accordance with the Declaration of Helsinki. Written informed consent was obtained from all participants prior to any study-related procedures. A Data Safety Monitoring Board (DSMB) oversaw participant safety throughout the trial (Supplementary Materials).

### 2.2. Protocol Amendment

Two protocol amendments have been made. The first amendment was made on 25 September 2020, which allowed the inclusion of participants with and without T2DM. This amendment was introduced to align with the results of the Study to Evaluate the Effect of Dapagliflozin on the Incidence of Worsening Heart Failure or Cardiovascular Death in Patients With Chronic Heart Failure (DAPA-HF) trial, in which dapagliflozin was shown to reduce cardiovascular events (including worsening heart failure and cardiovascular death) in both patients with and without diabetes [6]. Notably, this amendment was implemented prior to the start of patient screening and enrollment.

The second amendment, dated 18 June 2021, was made to harmonize the selection criteria with the Dapagliflozin Effects on Cardiometabolic Outcomes in Patients with an Acute Heart Attack (DAPA-MI) trial by adjusting the screening criteria to include patients with a left ventricular ejection fraction (LVEF) of ≤50% [7]. Additionally, the window for performing baseline CMR was extended to up to 15 days after the index event. This amendment was implemented after the enrollment of only three patients.

### 2.3. Patient Eligibility

The participants in the study had to meet all of the inclusion criteria. Those who met any of the exclusion criteria were not enrolled in the study.

#### 2.3.1. Inclusion Criteria

Patients between 30 and 85 years of age.Patients with a first myocardial infarction with ST-segment elevation, documented in an ambulance or a cardiac catheterization laboratory (ST-segment elevation ≥2 mm in at least two contiguous leads) <12 h after the onset of symptoms that last ≥20 min, undergoing primary percutaneous cardiac intervention. The target lesion must be a de novo lesion located in a native vessel.The patient understands and accepts clinical monitoring and CMR.The patient must be hemodynamically stable (Killip classification 1) at the time of the initial CMR.A left ventricular ejection fraction ≤50% at baseline echocardiogram.

#### 2.3.2. Exclusion Criteria

Pregnancy or lactation in women.Type 1 diabetes mellitus.Previous treatment with SGLT2is.Severe liver disease (Child-Pugh C).Kidney disease defined as stage III or worse (eGFR < 45 mL/min).Systolic blood pressure <90 mmHg at the screening visit.Malignancy (receiving active treatment) or other life-threatening diseases.Any contraindication to CMR (e.g., claustrophobia; cerebrovascular implants; metal implants; penetrating eye injury; exposure to metal fragments in the eye that require medical attention; or hemodynamic or electrical instability).Previous complicated urinary tract infection in men or repeated urinary infection in women.Treatment with fibrinolytic therapy.

### 2.4. Screening

Transthoracic echocardiograms were performed during routine clinical care for participants presenting with their first clinically diagnosed STEMI undergoing primary PCI to identify those with an LVEF ≤ 50%, measured by Simpson’s Biplane or estimated by visual assessment. Participants meeting the inclusion criteria and none of the exclusion criteria were approached by study investigators at each site to obtain consent. Consenting participants underwent a baseline CMR scan. Participants with an LVEF ≤ 50% on CMR were randomized, while those with an LVEF > 50% were excluded. To minimize the influence of baseline myocardial fibrosis developed before randomization, being maximal between 2 and 8 weeks after the index event [8], the baseline CMR was required to be performed within 15 days following STEMI, preferably before hospital discharge.

### 2.5. Trial Procedures

#### 2.5.1. Randomization and Blinding

Participants were randomized in a 1:1 ratio to receive dapagliflozin 10 mg daily (intervention) or a placebo (control). The randomization schedule was generated by an independent statistician using a computer-based program for stratified randomization, incorporating two stratification variables (i.e., presence of T2DM and infarction site) to ensure a balanced distribution across treatment groups. Participants were enrolled by the study investigators at each site after eligibility was confirmed and informed consent obtained. The trial pharmacist, who had exclusive access to the allocation codes, assigned participants to the intervention or control group. Randomization was stratified by the presence of T2DM (defined as an established diagnosis, glycated hemoglobin [HbA1c] ≥ 6.5% at index admission, fasting blood sugar ≥ 126 mg/dL, or 2 h blood sugar ≥ 200 mg/dL) and localization of the MI (anterior vs. non-anterior) [9]. Before randomization, baseline assessments were conducted, including weight and height measurement, a physical examination, a 12-lead electrocardiogram, standard laboratory tests (kidney function, liver function, HbA1c, full blood count), and biomarker sample collection. Randomization and administration of the first trial drug dose occurred within 24 h of the baseline CMR study.

The trial employed a quadruple-blind design to ensure that participants, care providers, outcome assessors, and data analysts were unaware of the treatment allocation. Emergency unblinding was permitted only in situations where knowledge of the participant’s allocation group was essential for managing a serious adverse event or a critical medical situation. The unblinding procedure required the treating physician to contact the trial pharmacist responsible for managing the randomization codes. The randomization code was disclosed solely for the specific participant, and the reason for unblinding was thoroughly documented and reported to the DSMB. Measures were taken to ensure that the study team remained blinded to the allocation, except the treating physician directly involved in the emergency management.

#### 2.5.2. Data Collection Plan

Study data were collected and managed using REDCap electronic data capture tools hosted at Hospital Clínic of Barcelona (redcap.clinic.cat). REDCap (Research Electronic Data Capture) is a secure, web-based software platform designed to support data capture for research studies, providing (1) an intuitive interface for validated data capture; (2) audit trails for tracking data manipulation and export procedures; (3) automated export procedures for seamless data downloads to common statistical packages; and (4) procedures for data integration and interoperability with external sources.

An anonymized and predefined electronic Case Report Form, developed by the investigators, was completed by each participating center. The selected variables focused on baseline characteristics, CMR parameters, biomarkers, medications, and outcomes (Table S1). The principal investigator and the trial statistician have access to the final dataset.

#### 2.5.3. Follow-Up Visits

After randomization, trial visits were scheduled at 1, 3, and 6 months, as outlined in Table 1. All visits were conducted in person. Participants were contacted regularly through scheduled follow-up visits, with reminders sent via telephone prior to each visit. If in-person visits were infeasible, telephone consultations and delayed laboratory sample collection were arranged. Medication adherence was assessed by counting pills at each follow-up visit. Outcome data, including CMR, were also collected for participants who discontinued or deviated from the protocol, when feasible.

All participants received standard post-MI care in accordance with international guidelines, including beta-blockers, angiotensin-converting enzyme inhibitors or angiotensin receptor blockers, statins, and dual antiplatelet therapy [10]. Participation in routine cardiac rehabilitation programs was encouraged. The use of diuretics and glucose-lowering agents was permitted when clinically indicated. Initiation of SGLT2is outside the trial protocol was prohibited. After the study ended, subsequent treatment was determined at the discretion of the treating physician for each participant.

#### 2.5.4. Cardiac Magnetic Resonance Imaging

CMR was performed at baseline and 6 months following randomization on a 3T scanner (ARCHITECT, General Electric, Milwaukee, Wisconsin, 53223, USA) equipped with a phased-array body surface coil and a cardiac-dedicated package with electrocardiogram gating. The following images were obtained within the study: conventional steady-state free-precession cine images covering the entire left ventricle on the short axis, with a slice thickness of 8 mm and no gap between slices, to calculate the indexed end-diastolic volume, indexed end-systolic volume, LVEF, and LV mass. T2 maps were obtained prior to contrast injection on the short axis. T1 maps were acquired before gadobutrol administration (0.2 mmol/kg, Gadovist^®^, Bayer Hispania, Barcelona, 08970, Spain) and 15 min later using a modified Look-Locker inversion-recovery sequence (MOLLI) with an embedded motion correction algorithm in the short-axis orientation at the basal, mid-ventricular, and apical levels, as well as in the four- and two-chamber views. Pre-contrast T1 maps were obtained using a 5-(3)-3 scheme, and post-contrast T1 maps were obtained with a 4(1)3(1)2 scheme. Late enhancement images were acquired 10 min after gadolinium administration using a standard ECG-gated T1-weighted segmented inversion-recovery gradient-echo sequence during repeated breath-holds in the same short axis locations and long axis views as for the cine images.

All scans were analyzed at a core laboratory facility (IDIBAPS Cardiac Imaging Group, Barcelona, 08006, Spain) by experienced cardiologists ([name] and [name]) in CMR postprocessing to generate a clinical report of the study. The scans were then pseudo-anonymized and analyzed by a single operator in accordance with the guidelines from the Society for Cardiovascular Magnetic Resonance and the European Society of Cardiovascular Imaging for reporting CMR examinations [11]. The baseline and 24-week scans were analyzed in pairs and side-by-side to minimize intra-observer variability, with the operator blinded to treatment allocation.

##### Native T1 and ECV Value Derivation

Whenever possible, three regions of interest (ROIs) of at least 1 cm^2^ were drawn in three distinct LV myocardial segments in the remote non-infarcted myocardium among the basal and midventricular slices, avoiding areas with image artifacts. Special attention was given to appropriate co-registration of the tracings between the baseline and follow-up studies to minimize interstudy variability and misregistration. The corresponding late-gadolinium enhancement short-axis images in the T1 maps were checked to avoid placing ROIs in areas with acute or chronic myocardial infarction. The mean values of all ROIs were labeled as the remote native T1 values for the baseline and follow-up studies. The mean myocardial ECVs for both baseline and follow-up studies were computed using the following formula:(1)$$ECV=\left(1-hematocrit\right)\times \left\lceil \frac{1}{Postcontrast\;T1my}-\frac{1}{Native\;T1my}\right\rceil ÷\left\lceil \frac{1}{Postcontrast\;T1bp}-\frac{1}{Native\;T1bp}\right\rceil$$
where postcontrast T1my is postcontrast myocardial T1; nativeT1my is native myocardial T1; postcontrast T1bp is postcontrast blood pool T1; and native T1bp is native blood pool T1.

LV Function, Volumes, and Infarct Size Calculations

Circle Cardiovascular Imaging 42 Medical Image post-processing software for Cardiac Magnetic Resonance, Version 5.12.1 (Calgary, Alberta, Canada), was used for these calculations. Briefly, an artificial intelligence-based algorithm automatically delineated the endocardial and epicardial contours at end-systole and end-diastole. Manual corrections were performed, if necessary, to compute the LV end-systolic and end-diastolic volumes and LVEF.

The infarct zone was quantified semi-automatically. Initially, the region with the highest signal intensity in the infarct core was identified, and the infarcted tissue was defined as the area with signal intensity above 50% of the maximum pixel intensity (full width at half maximum intensity method). Regions of microvascular obstruction were included in the quantification. Finally, the infarcted areas were summed and divided by the total mass of the left ventricular wall to calculate the infarct size as a percentage of the total LV mass.

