### 2.6. Trial Outcomes

The primary, secondary, and exploratory outcomes will be measured as the change from baseline to 6 months of follow-up (Figure 1). Differences between the dapagliflozin and placebo groups in these changes will be analyzed. All CMR measurements will be indexed to body surface area, calculated at the time of the scan using the Mosteller formula.

*Primary outcome*

The primary endpoint is the change in ECV of the remote myocardium from baseline to six months, as measured by CMR.

*Secondary outcomes*

These include changes in the circulating biomarkers from baseline to six months: C-terminal propeptide of type I procollagen;N-terminal propeptide of type III procollagen;Galectin-3;High-sensitivity troponin I.

*Exploratory outcomes*

The exploratory outcomes include changes in other CMR measures of cardiac function and remodeling from baseline to six months, including: Left ventricular end-diastolic and end-systolic volumes;Left ventricular mass;Left ventricular ejection fraction.

They also include changes in other circulating biomarkers from baseline to six months and clinical events:N-terminal pro-B-type natriuretic peptide.Suppression of Tumorigenicity 2.Rate of major adverse cardiovascular events (MACE), including cardiovascular death, non-fatal myocardial infarction, non-fatal stroke, and heart failure hospitalization. All these endpoints will be adjudicated independently by a clinical event committee (CEC) (Supplementary Materials).Adverse events (AEs) and serious AEs were actively collected at follow-up visits and through spontaneous reporting by participants during the study. AEs of interest were represented by severe hypoglycemia, acute kidney injury, acute liver function profile impairment, severe dehydration, symptomatic and sustained hypotension, complicated genitourinary infections, diabetic ketoacidosis, and diabetic foot complications (in diabetic patients). AEs were recorded using a standardized form and assessed for severity, causality, and expectedness. All adverse events were communicated to the DSMB.Change in body weight from baseline to six months.

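### The exploratory comparisons of LV volumes and LVEF use tests that take no covariate, so precision available from baseline infarct size is given up (minor)

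*Protocol article*

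**What the plan says.** - **Measurement.** The imaging part of section 2.5.4, under LV function, volumes and infarct size, gives a full method for infarct size: full width at half maximum, with microvascular obstruction counted in. It ends: "Finally, the infarcted areas were summed and divided by the total mass of the left ventricular wall to calculate the infarct size", expressed as a percentage of LV mass.
- **Timing.** Section 2.5.4: "CMR was performed at baseline and 6 months following randomization on a 3T scanner". Section 2.5.1 places randomization and the first dose within 24 hours of the baseline scan, so the baseline image cannot be affected by treatment.
- **Reading.** "The baseline and 24-week scans were analyzed in pairs and side-by-side to minimize intra-observer variability", by an operator blinded to allocation.
- **Outcomes.** Section 2.6 lists the exploratory CMR outcomes as changes in "Left ventricular end-diastolic and end-systolic volumes;Left ventricular mass;Left ventricular ejection fraction". Infarct size is not named, but the list is open-ended.
- **Analysis.** Section 3 fixes a Student's t-test or a Mann–Whitney test for the primary outcome, adds a mixed model for repeated measures as a sensitivity analysis, and extends similar methods to the exploratory outcomes. It names no covariates. Detail is left to an analysis plan to be finalized before database lock and unblinding.
- **Stratification.** Section 2.5.1 stratifies by type 2 diabetes and by anterior versus non-anterior infarction, not by infarct size.

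**The concern.** The introduction says that focal scar, like diffuse fibrosis, contributes to ventricular dysfunction. On the article's own reasoning, then, the amount of scar at baseline should carry information about how LV volumes and LVEF develop. The trial measures it before allocation, yet the main test stated for these outcomes has no place for it.

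What is at stake is precision. The trial stopped at 54 of 120 planned patients, so any variance that a baseline measurement can remove is worth more than it would have been at full size. Leaving it in widens the confidence intervals for the only outcomes that address the ventricular-function part of the aim.

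**Working it through.** **1. The plan's own figures.** Section 3 gives a placebo change of 1.5 with SD 2.2 and an 85% relative reduction, so the difference is 0.85 × 1.5 = 1.275.

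- Per arm for 80% power, two-sided 0.05: 2 × (1.96 + 0.84)² × (2.2/1.275)² ≈ 46.7, so 47. The article says 47.
- Power at 27 per arm: 55.2% (noncentral t). The article says 55%.

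The figures reproduce. They concern remote ECV only, and the present point does not depend on them.

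**2. What the stated test allows.** A t-test or Mann–Whitney test on the change score uses the outcome and the arm and nothing else. The mixed model could hold covariates, but it is the sensitivity analysis.

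**3. What adjustment would gain.** Let R² be the share of the variance of the outcome explained by baseline infarct size. The article does not give it; 10 to 30% is an assumed range. With n = 54 and 27 per arm:

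- residual variance is multiplied by (1 − R²);
- equivalent sample size = 54/(1 − R²);
- difference detectable with 80% power, in SDs of the outcome = (1.96 + 0.84) × √(2/27) × √(1 − R²) = 0.762 × √(1 − R²).

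| R² (assumed) | Equivalent n | Detectable difference (SD) |
|---|---|---|
| 0 | 54 | 0.76 |
| 0.1 | 54/0.9 = 60 | 0.72 |
| 0.2 | 54/0.8 = 67.5 | 0.68 |
| 0.3 | 54/0.7 = 77 | 0.64 |

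The cost is small: one covariate uses one of the 52 residual degrees of freedom (54 − 2), about 2%.

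**4. What chance imbalance means here.** The 95% range of a chance difference in mean infarct size is ±1.96 × √(2/27) = ±0.53 SD of infarct size. A difference of at least 0.5 SD arises in about 6.6% of trials with 27 per arm, against 0.6% with 60 per arm. These figures ignore stratification by location.

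Carried to the outcome, an imbalance of 0.53 SD shifts the comparison by r × 0.53, where r = √R²:

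- R² = 0.1: 0.32 × 0.53 = 0.17 SD of the outcome;
- R² = 0.3: 0.55 × 0.53 = 0.29 SD.

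The ordinary 95% half-width of the unadjusted comparison is itself 1.96 × √(2/27) = 0.53 SD. The shift is one component of that interval, not an addition to it. Adjustment removes that component.

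**5. Limits of the calculation.** The table compares adjustment for infarct size with no adjustment at all. Part of the same variance may be captured by infarct location and by the baseline value of the outcome, so the further gain from infarct size in a model that already holds those would be smaller. Losses to follow-up reduce both sides in proportion: with the 20% loss that section 3 allows for, 54 becomes about 43, and the equivalent sizes become 43.2/0.9 = 48 to 43.2/0.7 = 62.

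**The case against.** The strongest case against is that nothing is wrong. Randomization makes the unadjusted comparison valid, and its confidence interval already reflects chance imbalance. The outcomes are exploratory. Randomization is stratified by infarct location, and entry is limited to an LVEF of at most 50% on CMR, which may narrow the spread. The covariates of the mixed model may properly sit in the analysis plan, which is not shown. R² is assumed, so the 60 to 77 follows from the range chosen.

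All of that stands, and it keeps the point small. It does not remove it: the article does state the main type of test, that type cannot adjust, and a pre-randomization measurement is available.

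Three stronger readings are tempting, and the article does not support them.

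- **That imbalance in infarct size biases the ventricular comparison.** If infarct size had an SD of 8 to 12% of LV mass (assumption), the 95% range would be ±4.3 to ±6.4 points, which looks alarming. Step 4 of the working shows that it is ordinary sampling error, already within the stated interval.
- **That half of the fibrosis question goes unanswered.** The introduction says that these patients "experience both focal replacement fibrosis in the region of the MI and diffuse interstitial fibrosis in the remote myocardium", and that the trial "aims to assess the effect of dapagliflozin on myocardial fibrosis and ventricular function in patients presenting with their first clinically diagnosed STEMI", without limiting this to remote tissue. But it gives the evidence gap as "the effects of SGLT2is in remote myocardial fibrosis and ventricular function in patients with STEMI", and the primary endpoint matches that. Remote regions of interest are deliberately kept out of scar: the late-enhancement images "were checked to avoid placing ROIs in areas with acute or chronic myocardial infarction". At most, the aim is loosely worded.
- **That any later analysis of infarct size must be post hoc.** The exploratory list is open, section 4.4 says that no analysis has been done, and the analysis plan can still name it. That infarct size is quantified at six months is itself an inference from the scan schedule and the paired reading. The article gives no time point for it.

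**Conclusion.** The point holds as a matter of precision and is minor. For LV volumes and LVEF, the stated main test gives up information from a baseline measurement that the trial already takes. If that measurement explains 10 to 30% of outcome variance, adjustment is worth about 60 to 77 patients instead of 54, and the difference detectable with 80% power falls from 0.76 SD to between 0.72 and 0.64 SD. Both ranges rest on the assumed R² and are before any allowance for stratification by location or adjustment for the baseline outcome. The unadjusted comparison is not biased, no stated figure is wrong, and the primary and secondary analyses are unaffected.

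**What to change.** Before unblinding, state in the analysis plan that changes in LV volumes and LVEF are compared by ANCOVA, or by the mixed model already planned, with these covariates: baseline infarct size (% of LV mass), the baseline value of the outcome, diabetes status and infarct location. The t-test or Mann–Whitney result can be kept as a supporting analysis.

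The plan should confirm that the infarct-size value entered is the one from the baseline scan, and say how a patient without a readable value is handled.

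Optional: if infarct size is also quantified at six months, list its change as an exploratory outcome; otherwise word the aim as remote (diffuse) fibrosis.

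The cost is a few lines of text, a few residual degrees of freedom and, if the option is taken, one more exploratory outcome. The covariate needs no new scan and no new measurement method.
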